### Statistical considerations

#### Sample size calculation

The sample size calculation (GPower software version 3.1.3, University of Düsseldorf, Germany) was based on the Wilcoxon–Mann–Whitney test (two groups, two tailed). The calculation was based on the expectation that the primary endpoint variable (time from randomization to successful extubation) would show a difference of 2 days between the two treatment groups. Based on the study by Lellouche *et al*. [14] the standard deviation (SD) was estimated as 5 days for both groups, yielding an effect size (*d*) of 0.4. Accordingly, 104 patients per group would allow the detection of differences between the groups with a power of 80% and a type one error rate of 5%. Assuming that 10 dropouts per group may occur, 228 patients in total are necessary.

#### Statistical analysis

The descriptive analysis will include the mean and standard deviation for normally distributed variables. Variables that are not normally distributed will be expressed by their medians and interquartile ranges. Categorical variables will be expressed as *n* (%). Differences in the primary endpoint variable, time from randomization to successful extubation between the two treatment groups, will be analyzed by a Wilcoxon–Mann–Whitney test.

To decide on the proper comparison method for the exploratory analysis of the secondary endpoints, we will test whether the variables are normally distributed. Student’s *t*-test will be used to test groups of independent continuous normally distributed variables. The Mann–Whitney *U* test will be used for continuous variables that are not normally distributed. Categorical variables will be compared with the chi-square test or Fisher’s exact test. Paired data will be analyzed using Student’s *t*-test for continuous normally distributed variables, the Wilcoxon test for continuous variables that are not normally distributed and the McNemar or Bowker test, as appropriate, for categorical variables.

Kaplan–Meier survival curves will be computed to evaluate differences in overall survival. Survival curves will be compared by a log-rank test and multivariable analysis will be accomplished by the Cox regression model.

If any patients are lost to follow-up or withdraw consent for the trial, the reasons will be reported. The intention-to-treat (ITT) analysis and per protocol (PP) analysis will be conducted to test whether the result of this trial is reliable. Missing data will be handled by means of the last-observation-carried-forward method. For the intention-to-treat analysis, data will be processed for all trial patients in the groups to which they were randomized, regardless of whether they received or adhered to the allocated intervention.

It is assumed that the majority of patients in the two triage arms will receive the appropriate study intervention. The per protocol analysis will be performed as a secondary analysis if there are sufficient patients in the triage arms who do not receive study therapy or are lost to outcome assessment. Data from participants who do not violate the treatment protocols will be included in the per-protocol analysis.

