### Study endpoints

The primary endpoint is weaning time, defined as the time from randomization to successful extubation.

Secondary endpoints are: total time of mechanical ventilation; time from randomization to first extubation; time from randomization to fulfillment of extubation criteria; time between fulfillment of extubation criteria and extubation; ICU length of stay, in-hospital length of stay; ICU and in-hospital-mortality; mortality at day 90 and 6 months; PaO_2_/FiO_2_; PaCO_2_; total minutes of ventilation; mean tidal volume; mean pressure support; mean airway pressure; mean peak inspiratory pressure; inspiratory airway occlusion pressure at 100 ms; visual analogue scale for breathing comfort; cumulative amount of sedative and analgesic drugs; SOFA score; re-intubation rate; use of non-invasive ventilation; post-extubation duration of NIV; ventilator-free days (28 days); number of changes in mean pressure support by ICU personnel; coefficients of variation of tidal volume and pressure support; respiratory rate, and inspiratory and expiratory times.

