The ViPS trial will broaden our knowledge of the impact of variable PSV on important clinical outcome variables in a mixed ICU population. The inclusion and exclusion criteria have been carefully designed to include a large number of patients, regardless of their co-morbidities, while taking safety issues into account. Thereby, the use of variable PSV, which has been evaluated only for hypoxemic lung failure, will be expanded to other patient groups. The protocol described here represents a consensus among centers and investigators with considerable experience in weaning patients from mechanical ventilation. The interventions are an agreement between several weaning strategies conducted in the participating centers, while the variable PSV settings have been carefully derived from experimental knowledge combined with clinical experience. Therefore, compliance of the participating centers to the protocol is likely.

The ViPS trial protocol has limitations that must be addressed. First, the entry criteria allow for patients with large differences in weaning duration, ranging from hours to days. These differences have been considered in the sample size calculation. Second, patients who fail to wean may be transferred to weaning centers, resulting in them being lost to follow-up and, consequently, causing a reduction in study power. Nevertheless, the dropout rates considered in the sample size calculation represent a worst case scenario for the participating centers. Third, the protocol cannot be conducted in a blinded fashion, which can favor bias. To minimize this effect, we defined a tight protocol where intervention steps mandate handling until the primary endpoint is achieved. Fourth, even though the protocol interventions represent a consensus among centers, local differences in weaning experience and standards may still affect the results of this trial. Fifth, the use of non-invasive ventilation following extubation could introduce bias in terms of a reduction of weaning time, but this effect should not affect the comparative performance of variable PSV, since it is also allowed in the control group.

In conclusion, ViPS is the first randomized controlled trial that compares variable with non-variable PSV with respect to the duration of weaning from mechanical ventilation in a mixed ICU population. This trial may also clarify how and why variable PSV improves lung functional variables, and reduces the respiratory drive.

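### The unrestricted LOCF rule does not exempt vital status, so read literally it counts every patient lost to follow-up as alive in day-90 and 6-month mortality

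*Protocol article*

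**What the plan says.** The missing-data rule is one sentence in the Statistical analysis section: "Missing data will be handled by means of the last-observation-carried-forward method". It names no endpoint and excludes none.

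The secondary endpoints include "ICU and in-hospital-mortality; mortality at day 90 and 6 months". For categorical endpoints the analysis section gives counts with percentages, and then "Categorical variables will be compared with the chi-square test or Fisher’s exact test". For death over time it adds "Kaplan–Meier survival curves will be computed to evaluate differences in overall survival", followed by "Survival curves will be compared by a log-rank test and multivariable analysis will be accomplished by the Cox regression model". It writes no censoring rule. For patients lost or withdrawn it promises only that reasons will be reported.

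After discharge, the Follow-up section describes telephone contact at 28 days, 90 days and 6 months, with quality of life as its stated purpose. The Discussion names a likely cause of loss: "patients who fail to wean may be transferred to weaning centers, resulting in them being lost to follow-up".

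**The concern.** LOCF assumes that a value stays where it was last seen. For vital status this cannot work, because the last observation of a patient who is lost can only be alive. The rule therefore turns unknown status into survival, and the error has one direction.

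The expected losses may also not be a random subset. Patients who fail to wean are plausibly at higher risk of death, and they are the ones the Discussion expects to lose. Successful weaning is what the intervention aims to change, so loss could differ between arms.

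At stake are the reported day-90 and 6-month mortality in an open trial of a new ventilation mode, and whether these proportions agree with the trial's own survival curve.

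**Working it through.** **Inputs from the article.** Sample size calculation: 104 per group plus 10 dropouts per group, that is 114 per group and 2 × 114 = 228 in total, as stated. The dropout share is 10/114 = 8.8%. No mortality rate and no rate of missing vital status is given, so every mortality figure below is an assumption, and so is the use of the dropout figure as a loss rate.

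**Size of the understatement.** If a share *f* of a group is lost alive and a fraction *q* of those patients die before the time point, LOCF misses exactly *f* × *q*.

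*Case 1: loss unrelated to prognosis.* Assume a constant hazard over 180 days, 6-month mortality *p*, and 10 of 114 lost alive at day *L*. Then *q* = 1 − (1 − *p*)^((180 − *L*)/180).

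| *p* | *L* (days) | *q* | understatement = 10/114 × *q* |
|---|---|---|---|
| 20% | 28 | 0.172 | 1.5 points |
| 20% | 90 | 0.106 | 0.9 points |
| 30% | 28 | 0.260 | 2.3 points |
| 30% | 90 | 0.163 | 1.4 points |
| 40% | 28 | 0.350 | 3.1 points |
| 40% | 90 | 0.225 | 2.0 points |

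*Case 2: the lost may differ from those followed.* Assume 30% mortality in the 104 followed. LOCF reports 0.30 × 104/114 = 27.4%. The true figure is (0.30 × 104 + *q* × 10)/114.

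| *q* in the lost | true | LOCF | understatement |
|---|---|---|---|
| 30% | 30.0% | 27.4% | 2.6 points |
| 50% | 31.8% | 27.4% | 4.4 points |
| 70% | 33.5% | 27.4% | 6.1 points |

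The standard error of one arm's proportion is √(*p*(1 − *p*)/114), about 4.3 to 4.4 points at these true rates. Counting all 10 lost patients as dead would give (31.2 + 10)/114 = 36.1%.

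**Effect on the comparison.** Take equal true mortality of 31.8% in both arms, 50% mortality in the lost, and 20 losses in total. LOCF then reports 31.8% minus 0.5 × losses/114 in each arm. At 5 v 15 this is 29.6% v 25.2%, a difference of 4.4 points. Exact rejection rates at the nominal 5% level, from the binomial distribution of observed deaths in each arm:

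| losses | chi-square, uncorrected | Fisher |
|---|---|---|
| 5 v 15 | 11.1% | 8.3% |
| 6 v 14 | 8.7% | 6.4% |
| 8 v 12 | 5.7% | 3.9% |
| 10 v 10 | 4.6% | 3.1% |

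Inflation therefore needs clearly unequal loss. At the planned equal loss there is none.

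**The case against.** A reader might infer that the protocol sets two conflicting rules for the same deaths and that the conflict biases the proportions. The text does not support that. It never says that LOCF applies to mortality and it writes no censoring rule; both are read from general sentences and from the choice of Kaplan-Meier. A crude proportion and a survival curve are often reported together. Any downward bias comes from LOCF alone.

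A reader might also infer that the trial will produce a spurious mortality difference. That needs unequal loss, which nothing in the article predicts.

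Other objections stand in part:

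- The 10 dropouts per group are budgeted for weaning time, and the Discussion calls that rate a worst case. A dropout for weaning time may still have known vital status through the telephone contacts. The sizes above are therefore conditional.
- That the lost are sicker is plausible but not stated; the Discussion says only that such transfers may happen.
- Kaplan-Meier is not a clean reference. If the lost are sicker, censoring is informative and the curve also understates mortality. In the 5 v 15 case, mortality among those followed is 30.9% v 29.0%, against a true 31.8% in both arms. This argues for a sensitivity analysis and does not defend LOCF.
- The secondary endpoints are expressly exploratory.

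The objection that a condensed article leaves such detail to the full protocol or SAP does not dispose of the point. The article does not leave missing data open. It states a rule, and an analysis plan faithful to that rule would inherit the error.

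**Conclusion.** The point holds in a limited form. Followed as written, the LOCF rule carries survival forward for every patient with unknown vital status, so it can only understate day-90 and 6-month mortality, and it would not match the usual handling of the same patients in the Kaplan-Meier analysis.

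If 10 of 114 per group were lost, the understatement is about 1 to 3 points with loss unrelated to prognosis, which is below one standard error of a single arm's proportion. It is about 4 to 6 points, or 1.0 to 1.4 standard errors, if the lost die at 50% to 70% against 30% in those followed. These sizes rest on assumed mortality and a borrowed loss rate; the direction does not. A false difference between arms is a risk only if loss is clearly unequal. The primary endpoint analysis is not touched by this point.

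**What to change.** In the Statistical analysis section, state that LOCF does not apply to vital status. Estimate day-90 and 6-month mortality by Kaplan-Meier at those times, censor lost patients at the date last known alive, and give the difference between arms with a 95% confidence interval. Because loss may be informative, add one sensitivity analysis that counts lost patients as dead.

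The cost is a sentence or two in the plan and one extra table, with no new data items beyond the date last known alive. The downside is slightly wider intervals and somewhat higher reported mortality.

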### Extubation criteria

As the ventilator settings are reduced in a stepwise manner to reach the extubation criteria, the patient’s condition is continuously monitored. As soon as the patient fulfills the following extubation criteria for a time period of at least 30 minutes, extubation is possible:

Richmond agitation and sedation scale (RASS) ≥ −3; behavioral pain scale (BPS) ≤5 or visual analogue scale (VAS) for pain ≤3; raising hands or legs against gravity; temperature ≥36°C and ≤39°C; ability to cough to clear secretions after deflating cuff; respiratory rate 8 to 30/min; PaO_2_/FiO_2_ ≥ 200 mmHg (≥150 mmHg in patients with chronic obstructive pulmonary disease); pressure support ≤8 cmH_2_O; PEEP ≤8 cmH_2_O; systolic blood pressure 80 to 160 mmHg; heart rate 40 to 130/min and no hemodynamically relevant arrhythmia.

If extubation has occurred and the patient needs to be re-intubated within 72 hours, the extubation is defined as not successful and the assigned study mechanical ventilation mode will be reinstituted as soon as possible. Successful extubation is defined as extubation lasting 72 hours.

Non-invasive ventilation (NIV) after extubation is allowed after extubation according to local practice. However, if a PEEP level >8 cmH_2_O, or pressure support >8 cmH_2_O is required for NIV, the extubation is considered not successful.

If the patient has to receive tracheotomy during the study period, assisted mechanical ventilation will be resumed as soon as possible via the tracheal cannula according to the assigned therapy group. In tracheotomized patients successful extubation is defined as patient separation from the ventilator without reconnection for <72 h after separation. If continuous positive airway pressure (CPAP) therapy via the tracheal cannula with PEEP >8 cmH_2_O or pressure support >8 cmH_2_O is required, the separation from the mechanical ventilator is considered not successful. The study-related intervention is finished on successful extubation. Patients will be observed until ICU and hospital discharge and contacted during the follow-up period.

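### The primary rank test needs a weaning time for every randomised patient, but the only missing-data rule, unrestricted LOCF, gives no valid value for a patient who dies or is transferred while still ventilated

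*Protocol article*

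**What the plan says.** All of this is in the protocol article.

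- **Endpoint** (Study endpoints): "The primary endpoint is weaning time, defined as the time from randomization to successful extubation".
- **What counts as the event** (Extubation criteria): "Successful extubation is defined as extubation lasting 72 hours". A patient who dies on the ventilator never reaches it.
- **Primary test** (Statistical analysis): the endpoint "will be analyzed by a Wilcoxon–Mann–Whitney test". Neither censoring nor a competing event is mentioned for it.
- **Analysis set** (Statistical analysis): for intention to treat, "data will be processed for all trial patients in the groups to which they were randomized".
- **Missing data** (Statistical analysis): "Missing data will be handled by means of the last-observation-carried-forward method". No endpoint is excepted.
- **Survival methods** (Statistical analysis): "Kaplan–Meier survival curves will be computed to evaluate differences in overall survival". The log-rank test and Cox model follow in that same context, not for weaning time.

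The article foresees patients without a weaning time. Mortality in the ICU, in hospital, at day 90 and at 6 months is a secondary endpoint. The limitations in the Discussion say that patients who fail to wean may move to weaning centers and be lost, and treat this only as a loss of power.

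**The concern.** A Wilcoxon–Mann–Whitney test needs one rankable value per patient. The article fixes the test, the analysis set and the imputation rule, and together they supply no such value for a patient who dies ventilated, is transferred ventilated or never weans.

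Three readings fit the text:

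1. The last time seen on the ventilator is carried into the weaning-time field. Death on day 2 then becomes a weaning time of 2 days.
2. Patients without a weaning time are left out. This selects on an outcome that arises after randomisation and contradicts the intention-to-treat statement.
3. LOCF is meant only for the daily measurements. The primary endpoint then has no rule at all.

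Under the first two, a ventilation mode with more deaths before weaning tends to look faster. The same holds for transfers: an unweaned patient scored at the last observation looks like an earlier success. The trial is open-label, so a choice among these readings made after data are seen would be hard to defend.

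**Working it through.** **1. The plan's own figure.** The inputs in Sample size calculation are a difference of 2 days, an SD of 5 days, two-sided 5% error and 80% power. The effect size is d = 2/5 = 0.4. Noncentral-t power with the Wilcoxon–Mann–Whitney efficiency for a normal parent (3/π = 0.955) gives 104 per group at power 0.801, as stated. The total is 2 × (104 + 10) = 228, also as stated. The arithmetic is right, but it presumes a weaning time for everyone analysed.

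**2. Model for the size of the bias.** The article gives no mortality on the ventilator and no distribution of weaning times, so these are assumptions:

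- Weaning is exponential with mean 5 days in both arms, so there is no true effect on weaning.
- The death hazard is constant, set so that a proportion p dies before weaning.
- There are 114 patients per arm.

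Under this model the time to the first of weaning or death is exponential with mean 5(1 − p). More deaths therefore shorten the scored time directly. For example, a death on day 2 ranks ahead of exp(−2/5) = 67% of weaning times.

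**3. Formula for time-of-death scoring.** Let p be the death proportion in the lower-mortality arm and q that in the other. The probability that a random patient from the higher-mortality arm has the shorter scored time is

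θ = (1 − p) / [(1 − p) + (1 − q)].

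The null standard error of the rank statistic on this scale is √[(2n + 1)/(12n²)] = √[229/(12 × 12,996)] = 0.0383. The chance of a significant result favouring the higher-mortality arm is about P(Z > 1.96 − (θ − 0.5)/0.0383).

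| Deaths before weaning | θ | (θ − 0.5)/0.0383 | Formula | Simulation, time-of-death scoring | Simulation, deaths excluded |
|---|---|---|---|---|---|
| 15% vs 15% | 0.500 | 0 | 2.5% | 2.6% | 2.7% |
| 15% vs 18% | 0.509 | 0.23 | 4.2% | 4.2% | 4.0% |
| 15% vs 20% | 0.515 | 0.40 | 5.9% | 5.6% | 5.3% |
| 10% vs 20% | 0.529 | 0.77 | 11.7% | 11.6% | 10.6% |
| 15% vs 30% | 0.548 | 1.26 | 24.3% | 24.4% | 19.6% |

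The nominal rate is 2.5%. The simulation used 20,000 trials per row. Exclusion does nearly as badly because, in this model, the weaning times of those who do wean have the same shortened distribution; only the numbers are smaller.

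**4. Ranking deaths worst.** In the last two rows, the chance of favouring the higher-mortality arm falls to 0.3% and below 0.1%. The test instead goes against that arm in 11% and 23% of trials.

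**5. A different shape.** With gamma weaning times (mean 6, SD 5; 3,000 trials), time-of-death scoring favours the higher-mortality arm in 13% of trials for 10% vs 20% and 44% for 10% vs 30%. Exclusion gives 9% and 25%. With 10% in both arms, time-of-death scoring stays at 2.5%.

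**The case against.** **The article does not say that deaths are scored as early weaning.** A reader might infer that a patient who dies on the ventilator is ranked as a quick success. No sentence classes death as missing data or turns the time of death into a weaning time. Weaning time is one value with no earlier measurement to carry forward, and LOCF fits the daily measurements naturally. This objection stands. The defect is that the one stated rule has no valid meaning here; the harmful scoring is only its literal reading.

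**Handling of death is often left to the analysis plan, which is not shown.** This stands for the details. It does not cover an LOCF rule written without exception beside a test that needs complete data.

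**Large mortality gaps between two forms of pressure support may be unlikely.** The entry criteria exclude expected survival under 72 hours and require a stability test. This stands in part: with small gaps the bias is small, and with equal mortality the error rate is nominal. Mortality endpoints, ventilator-free days and the safety board would help to reveal a large gap, but they do not correct the primary p-value.

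**Loss of power is not a good argument for the change.** This stands. Assuming mean weaning times of 5 vs 3.2 days and an equal death hazard giving 15% deaths in the control arm, power is 0.82 without deaths, about 0.72 with time-of-death scoring and about 0.74 with worst rank.

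**Conclusion.** The concern holds as a badly fixed rule: test, analysis set and LOCF together give no valid primary value for a patient who dies or is transferred before weaning. Neither literal carry-forward nor exclusion repairs this, and both tilt the result towards the arm with more deaths.

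The size depends on a mortality difference that the documents do not let one estimate. It runs from no inflation at equal death rates, through roughly double the nominal rate for a gap of 3 to 5 percentage points, to about ten times nominal at 15% vs 30%. These figures rest on constant hazards, death times unrelated to the patient's own weaning time, and no true effect on weaning. Bias from transfers is in addition and was not quantified. The sample size calculation itself reproduces and is not in question.

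**What to change.** 1. State that LOCF does not apply to the primary endpoint.
2. Keep the Wilcoxon–Mann–Whitney test, but rank death before successful extubation worse than every successful weaning.
3. Rank patients not weaned by a fixed horizon below all weaned patients, and state how they are ordered relative to deaths. Day 28 is a natural choice, because ventilator-free days to day 28 already require ventilation status. Day 90 is less suitable: the follow-up calls are described only as assessing quality of life, so weaning status at that point is not shown to be collected.
4. State how transfer while ventilated is handled, with a sensitivity analysis that varies the rank given to these patients.
5. Support the result with the cumulative incidence of successful extubation, with death as a competing event.

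**Cost.** This is mainly wording, since extubation times and mortality are already recorded. Status at the horizon must be sought for transferred patients. The endpoint is then read as being weaned alive and not as a pure duration. The sample size need not change for this.
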